#### Measurement of language/cognitive function

For the clinical evaluation of language and the rest of higher cognitive functions, subtests from the following batteries and neuropsychological tests are used:

- Revised Barcelona Test (TB-R) (42): battery of neuropsychological tests with the aim of assessing high cognitive functions.- WAIS-III Wechsler Adult Intelligence Scale (43): global intelligence scale for adults that allows for obtaining verbal, manipulative, and total intelligence quotients, as well as indicators of verbal comprehension, perceptual organization, working memory, and processing speed.- Trail Making Test (44): test used to assess visual attention, sequencing, flexibility, and graphomotor ability. It consists of two parts. In the first part, the subject must place numbers in order along a line; in the second part, the task is to place numbers and letters alternately, in an orderly way.- Continuous Performance Test-III (CPT-III) (45): computerized test that assesses sustained attention. The subject must press a key whenever a non-target letter appears (if the target is the letter “x,” it should not be pressed).- Rey Auditory Verbal Learning Test (46): test assessing auditory verbal memory. Fifteen words are read aloud to the subject, who is then asked to repeat as many words as they remember. The procedure is repeated four more times. After some time, a delayed recall of the list is made, and finally, a recognition test is carried out.- WMS-IV Wechsler Memory Scale (47): scale to assess memory functions.- Symbol Digit Modalities Test (46): test of attention and visual tracking, concentration, and psychomotor speed. An answer sheet divided into boxes is presented, in which the stimuli are made up of a sequence of geometric figures with a number assigned to each one. The subject must write the number corresponding to each figure in the relevant box, as quickly as possible.- PMR verbal fluency by letter (48): test assessing lexical access and verbal fluency, in which the subject is asked to say as many words beginning with “P” as they can, within 1 min. The same instructions are given for the letters “M” and “R”.- Hayling test (49): test that evaluates behavioral regulation, initiation speed, and response inhibition. In the first part, the subject is asked to complete a series of sentences as quickly as possible. In the second part, the subject must complete the sentence with a non-obvious word based on the context.- Wisconsin Card Sorting Test (50): test evaluating executive function, in particular mental flexibility and abstract reasoning. Four stimulus cards are presented, with different shapes, colors, and number of figures (categories). The subject must match each card in the deck with one of the four key cards (without being told how to do this). The participant only receives feedback on whether the match is correct or incorrect.

Bilingualism is tested by means of a questionnaire (51). Each participant is going to be self-rated on a 4-point scale on the abilities of comprehension, Reading, writing, fluency, and pronunciation for each language (1 = poor, 2 = regular, 3 = good, and 4 = perfect). In addition, a laterality test is included, the Edinburgh Handedness Inventory (52), as well as a questionnaire to assess anxiety and depression, the Hospital Anxiety and Depression Scale (53).

#### Neuroimaging

Magnetic resonance imaging (MRI) is acquired to assess anatomical and functional (fMRI activation maps) brain changes due to intervention and surgery. For instance, the development of novel activation sites distant from the surgical target may indicate that NICP was effective in promoting a reduction of functional relevance for targeted areas, in favor of a more distributed network. Therefore, all patients undergo three identical MRI sessions: (1) before NICP, (2) after NICP but before surgery, and (3) after surgery. Each session consists of MRI data acquisition using a 3 Tesla Siemens PRISMA scanner and a 32-channel head coil. The protocol includes accelerated multiband sequences adapted from the Human Connectome Project and provided by the Center of Magnetic Resonance Research (CMRR) at the University of Minnesota.

Regarding anatomical acquisitions, a high-resolution T1-weighted structural image is obtained with a magnetization-prepared rapid acquisition gradient-echo (MPRAGE) three-dimensional protocol, in which in an ascending fashion a total of 208 contiguous axial slices are obtained [repetition time (TR) = 2400 ms, echo time (TE) = 2.22 ms, inversion time = 1000 ms, flip angle = 8°, field of view (FOV) = 256 mm and 0.8 mm isotropic voxel]. In the same session, a high-resolution multishell diffusion-weighted MRI scan is obtained. This scan consists of two multiband acquisitions (anterior–posterior; acceleration factor = 4), sensitized in 99 monopolar directions with a b-value of 3000 s/mm2 in an echo-planar imaging sequence [TR = 3230 ms, TE = 89.20 ms, section thickness = 1.5 mm, voxel size = 1.5 × 1.5 × 1.5 mm, FOV = 210 mm].

In terms of quantifying brain function, resting-state and task functional MRI (fMRI) are acquired. Both consist of high-resolution multiband (anterior–posterior phase-encoding, acceleration factor = 8) interleaved acquisitions [T2^*^-weighted EPI scans, TR = 800 ms, TE = 37 ms, 750 volumes, 72 slices, slice thickness = 2 mm, FOV = 208 mm]. First, resting-state fMRI is acquired while the patient is instructed to keep his eyes closed and remain still without falling asleep.

Then, task fMRI is acquired during three language and three motor paradigms, which adhere to the following procedures:

- Word generation task: Block paradigm consisting of five cycles. Each cycle comprises 30 s of rest followed by 30 s during which the participant must mention words starting with a certain letter. These letters are “F”, “A”, “S”, “M”, and “E”, in this same order.- Semantic decision task: Block paradigm consisting of five cycles. Each cycle comprises 30 s of rest followed by 30 s during which the participant must mention objects from certain places: school, kitchen, car, house, and hospital.- Comprehensive auditory task: Block paradigm consisting of three cycles. Each cycle comprises a 30 s block, in which a story is narrated in a made-up language (inactive/rest block/condition), followed by another 30 s block, in which a story is narrated in Spanish (active block/condition).- Finger tapping task: Block paradigm consisting of three cycles. Each cycle comprises a 30 s block, in which the patient is asked to do a fingering exercise (tap each finger with the thumb) in the corresponding hand, followed by another 30 s of rest.- Ankle flexion task: Block paradigm consisting of three cycles. Each cycle comprises a 30 s block, in which the patient is asked to move the corresponding foot up and down slowly, followed by another 30 s of rest.- Tongue movement task: Block paradigm consisting of three cycles. Each cycle comprises a 30 s block, in which the patient is asked to move the tongue in circles without opening the mouth, followed by another 30 s of rest.

#### TMS for assessment and modulation of brain function

Neuromodulation by means of TMS is used for assessment and therapeutic purposes, to both non-invasively estimate the excitability and modulate the plasticity of the cerebral cortex (Figure 2).

**Figure 2 F2:**
[figure not shown]
Neuronavigated TMS mapping and neuromodulation. Example of Brainsight project developed for neuronavigated TMS mapping of motor and language functions (upper row) and for subsequent neuromodulation by means of low-frequency rTMS (lower row). In this case, a patient with subcortical frontotemporal tumor undertook NICP for language function, with the target of stimulation based on MNI coordinates of peak fMRI activity for ipsilesional semantic decision task. The overlays in fuchsia and beige are clusters of fMRI for word generation task and semantic decision task, respectively.

Typical assessments are single-pulse and paired-pulse protocols (54, 55). With single-pulse, it is possible to determine the resting motor threshold (RMT) and then measure contralateral peripheral response to suprathreshold motor evoked potentials (MEPs) during motor mapping of the upper limb, lower limb, and facial muscles. When a suprathreshold MEP is delivered over contralateral M1 during an isotonic muscle contraction, a cortical silent period (transient disruption of EMG activity) is visible immediately after the stimulus and is a measure of intracortical inhibitory circuitry. Other assessments of intracortical inhibition are investigated by paired-pulse protocols, such as short-interval and long-interval paradigms where the inter-stimulus interval is between 1–5 ms and 50–200 ms, respectively. By contrast, paired-pulse at intervals between 8 and 30 ms cause intracortical facilitation.

There are several paradigms of repeated TMS (rTMS) to promote neuroplastic changes (9, 56). Conventional rTMS has inhibitory effect at low frequency ( ≤ 1 Hertz) and excitatory effect at high frequency (>1 Hertz). For patterned (theta-burst stimulation, TBS) rTMS, inhibitory and excitatory effects result from continuous TBS and intermittent TBS, respectively. Stimulation parameters (stimulation intensity, number of pulses) and external factors (medications, drugs, mental status) may significantly alter or even reverse the effect of the neuromodulation (57, 58); therefore, treatment sessions should be performed in standard conditions and following specific protocol parameters.

#### Neurophysiological assessment

By performing neuronavigated TMS mapping, we compare the anatomical distribution of active targets pre- vs. post-intervention. The same targets and intensity of stimulation defined at baseline are used at the end of the intervention, to allow comparisons. A figure of 8 coil (MagPro Cool B65-AP-RO Coil) connected to a transcranial magnetic stimulator (MagVenture MagPro x100) is driven by a robotic arm (Axilum Robotics TMS-Cobot) controlled manually or through a dedicated neuronavigation software (Brainsight TMS neuronavigation). We apply biphasic current with an anterior–posterior followed by a posterior–anterior current direction in the brain; the TMS coil is held tangential to the scalp, the handle pointing backward with a 45-degree deviation from the sagittal plane. For curvilinear 3D brain reconstruction (MNI coordinates), participant's structural and functional MRI data are uploaded. Grids of targets (inter-target distance: 10 mm) are defined based on anatomical landmarks for the subsequent motor/language mapping protocol and to determine the hotspot for neuromodulation. Grids are placed in correspondence with the primary sensorimotor and premotor areas (motor mapping) and over the pars triangularis and the gyrus supramarginalis (language mapping).

The procedure for motor and language mapping (at baseline and at the end of the prehabilitation program) is as follows:

*Set up*. The patient is seated on an electromechanics treatment chair to ensure comfort and stability during the assessment. An optic tracker (Polaris Vicra) detects trackers for 3D localization of the Cobot, the patient (a Brainsight Adhesive Subject Tracker is attached to the patient's forehead), and the pointer (Brainsight P-970, for the registration of anatomical landmarks). After skin preparation (alcohol swab), self-adhesive electrodes for EMG recording are attached bilaterally to the olecranon (ground), the muscle belly of the first dorsal interosseus (FDI, negative electrode), and the muscle tendon of the FDI (positive electrode). A pillow is placed underneath the forearm of the side being assessed, to ensure that muscles are completely at rest during the protocol. PowerLab 8/35 and Quad Bio Amp (ADInstruments, data acquisition hardware devices) register the EMG response and send data to the dedicated software (ADInstruments, LabChart, data analysis software). Every time a TMS pulse is delivered, a trigger signal is sent automatically from the MagPro x100 to the PowerLab through a D-type 26-BNC interface cable, to initiate the recording of the EMG response. For language mapping, a screen for image presentation is placed in front of the patient. One computer runs Brainsight, while another computer runs LabChart and a dedicated MATLAB script for language mapping.

*Mapping protocol*. The whole protocol is performed for both the affected and unaffected sides. For motor mapping, the entire session is recorded in LabChart. A preliminary search of the hotspot is performed around the hand knob of the precentral gyrus, starting from an intensity of 35–40% and rising progressively up the intensity until stable MEPs (here defined as signals with peak-to-peak amplitude larger than 500 μV) are produced. Then, a formal hotspot search is performed, by applying five stimuli to each selected target; the target showing the largest average MEPs is considered the hotspot to determine the RMT, defined as the lowest intensity capable of eliciting three MEPs (signals with peak-to-peak amplitude larger than 50 μV) out of six consecutive stimuli (5- to 10-s interval). Once RMT has been determined, motor mapping is performed by applying five stimuli for each target (120% RMT intensity, 5- to 10-s interval) as far as positive MEPs (signals with peak-to-peak amplitude larger than 50 μV) are detectable.

For language mapping, a speech disruption protocol is applied. Initially, patients are familiarized with pictures and instructed to name them as soon as they appear on a screen in front of them. Once it is verified that the patient can name pictures correctly, we start language mapping. rTMS (five pulses at 5 Hertz, 90% RMT) is delivered to each target, together with presenting a picture on the screen (picture presentation time: 500 ms; delay picture-rTMS: 0 ms). The order of target stimulations and picture presentations is pseudo-randomized. An audio/video recording of the patient's response (from 0 to 3000 ms after the first rTMS stimulus) is evaluated offline by a neuropsychologist unaware of the target that has been stimulated to determine whether there was an episode of speech arrest, anomia, or other speech disruption phenomena. The language protocol is repeated until each target receives rTMS three times. A dedicated MATLAB script is developed to automatically synchronize rTMS with picture presentation and audio–video recording.

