### Primary and secondary outcomes

The primary outcome is the feasibility of the whole intervention, defined by the following parameters:

- Adherence to treatment: to define that the patient completed the protocol, at least 75% of the planned sessions should be performed.- Retention: successful retention rate is reached if at least 75% of enrolled participants complete the prehabilitation program.- Adverse events: absence of any adverse event attributable to the prehabilitation program, except for expected transient mild symptoms previously reported for neuromodulation (headache, syncope, and skin irritation) or motor training (mild pain and fatigue).- Patient's satisfaction: At the end of the protocol, participants fill out questionnaires evaluating the patient's satisfaction with the treatments received (13).

Secondary outcomes are related to exploratory analyses of the effectiveness and potential mechanisms of action of the proposed intervention. We investigate changes from baseline regarding clinical outcomes, fMRI, and TMS mapping. Notably, the goal of the intervention is to reduce the functional relevance of targeted areas because of compensatory activation of other brain resources within the same functional network. Slow-growing tumors already demonstrated that similar neuroplastic changes may occur, with the tumor mass progressively interfering with the functionality of critical areas, while remote brain areas increase their activation; such compensatory mechanisms may explain why these types of tumors are asymptomatic and without any functional deficits in the initial phases (14, 15). From this perspective, the prehabilitation program could be considered a method to artificially optimize and accelerate this neuroplastic adaptation for therapeutic purposes (3). Therefore, we do not expect significant changes regarding clinical outcomes, whereas we consider changes in neuroimaging and neurophysiology outcomes as indicators for the effectiveness of the prehabilitation program.

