#### Neuromodulation – Navigated rTMS

rTMS is applied with the following parameters: waveform: monophasic; intensity: 90% resting motor threshold (RMT); pulse frequency: 1 Hertz; total number of pulses: 1800. The choice of the target is determined based on anatomical considerations and results from neurophysiological and neuroimaging assessments; hence, the area of highest activity among those structures anatomically located near the tumor is considered the target. For instance, by performing motor and language mapping, we could identify active targets at the level of targeted areas, such as the hand knob or sites where speech arrest was detected. We also consider the center of mass of fMRI mapping related to hand movement and speech production as potential hotspots for neuromodulation.

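### Language-mapping rater: masking is stated for the stimulated target but not for the session, so the pre-post change in the number of active sites is open to drift in the rater's threshold

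*Protocol article*

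**What the plan says.** Under Neurophysiological assessment, language mapping by speech disruption is done at baseline and again at the end of prehabilitation. The recording of each response "is evaluated offline by a neuropsychologist unaware of the target that has been stimulated", whose task is "to determine whether there was an episode of speech arrest, anomia, or other speech disruption phenomena". On order and repetition the article says: "The order of target stimulations and picture presentations is pseudo-randomized", and "The language protocol is repeated until each target receives rTMS three times".

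The same section gives the use of these ratings: "we compare the anatomical distribution of active targets pre- vs. post-intervention". It standardizes the stimulation for that purpose: "The same targets and intensity of stimulation defined at baseline are used at the end of the intervention, to allow comparisons".

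Baseline mapping also has a role before treatment. The Figure 1 legend uses fMRI and TMS mapping at t0 to allocate patients to upper limb or language training. The section on navigated rTMS lists, among possible targets, active sites found by mapping, "such as the hand knob or sites where speech arrest was detected".

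Under Primary and secondary outcomes, clinical scores are not expected to change much; instead, "we consider changes in neuroimaging and neurophysiology outcomes as indicators for the effectiveness of the prehabilitation program". Table 1 describes a single-arm study.

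**The concern.** The stated masking and the stated inference concern different contrasts. A rater who does not know the target cannot favor one site over another within a session. That does nothing to keep the rater's calling threshold the same at baseline and after treatment. Targets and stimulation intensity are fixed across sessions; the rating is not.

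The rating is a judgement on a clip of 3 seconds and includes an open category of other disruptions. The trial has no concurrent control, and the hoped-for direction is declared: less functional relevance of the targeted areas. A rater who knew a clip came from after treatment and called slightly fewer disruptions would reduce the count of active sites without any change in the patient. The article counts neurophysiological change as evidence of effectiveness, so such a fall could be read as a treatment effect.

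**Working it through.** **Step 1: what is masked, and when scoring happens.**

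- Masked: the stimulated target. Pseudo-randomized order supports this within a session.
- Not stated: whether the rater knows the session, whether clips from both sessions are pooled or shuffled, and whether the rater is separate from the neuropsychologist who supervises language training.
- Sequence: a baseline language result that informs allocation or targeting must exist before the first treatment session. The post clips are recorded at t4. The two sets cannot have been mixed for that scoring, and no later re-scoring is described.

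**Step 2: effect on one site.** The article gives no figure to reproduce, so this is an illustration. From the article: 3 stimulations per target. Assumed: a target is active if at least 1 of 3 clips is called positive; the call rate per clip is p at baseline and p(1 − r) after treatment, with no true change. Then P(active) = 1 − (1 − p)³ at baseline and 1 − (1 − p(1 − r))³ after treatment.

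| p | baseline | r = 0.1 | r = 0.2 | r = 0.3 |
|---|---|---|---|---|
| 0.10 | 0.271 | 0.246 | 0.221 | 0.196 |
| 0.20 | 0.488 | 0.449 | 0.407 | 0.364 |
| 0.30 | 0.657 | 0.611 | 0.561 | 0.507 |

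Example: p = 0.20, r = 0.2 gives 1 − 0.80³ = 0.488 and 1 − 0.84³ = 0.407, a ratio of 0.83. Under a 2-of-3 rule the same inputs give 3(0.20²)(0.80) + 0.20³ = 0.104 and 3(0.16²)(0.84) + 0.16³ = 0.069: a larger relative fall (ratio 0.66) but a smaller absolute one.

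**Step 3: effect on the test.** A simulation with 1,500 runs per setting and no true change. The rater knows the session but not the target, so r applies equally everywhere. Assumed: half the targets near the tumor with call rate 0.30, half elsewhere with 0.15; 20 or 40 targets; 10 or 20 language-mapped patients; the 1-of-3 rule; threshold 0.05. From the article: two-sided Wilcoxon signed-rank test, and a sample size of 20. The table gives the chance of p<0.05 for the change in the number of active sites.

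| Patients / targets | r = 0 | r = 0.1 | r = 0.2 | r = 0.3 |
|---|---|---|---|---|
| 10 / 20 | 0.059 | 0.117 | 0.309 | 0.662 |
| 10 / 40 | 0.048 | 0.181 | 0.557 | 0.902 |
| 20 / 20 | 0.049 | 0.183 | 0.584 | 0.931 |
| 20 / 40 | 0.051 | 0.339 | 0.887 | 0.999 |

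For the change in the share of active sites that lie near the tumor, the chance of p<0.05 ran from 0.038 to 0.067 over all 16 settings, close to nominal. Effective masking to session corresponds to r = 0.

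**The case against.** The strongest reply is that a journal article condenses the protocol, and coding of recordings, rating order and assignment of raters are often left to the full document. Nothing stated is wrong in itself. That stands against saying that the rater knows the session: a reader might infer this, but the article is silent on it. It does not remove the point, because the article does choose to specify the masking, specifies it for the target only, and itself gives baseline mapping a use before treatment.

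A reader might also infer that the rater must know the session for every patient. That is not supported. Speech-arrest sites are one possible basis for the target; fMRI is another, and the language case in Figure 2 was targeted on an fMRI peak. Patients given tDCS or motor prehabilitation need not have language clips scored early. A different person could score the post clips, although that would bring in between-rater differences.

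The most substantive objection is that the named comparison is the anatomical distribution of active sites, not their total. To fake a shift away from the tumor, the rater would have to know which clips came from nearby sites, and target masking with pseudo-randomized order hides that. The simulation agrees, so the stronger reading, that expectation could readily produce a false reorganization, fails. Two limits remain. The article does not say how the distribution is summarized. And a uniform fall in calls also lowers the number of active sites in the targeted areas, which could be taken for the intended effect.

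Finally, every call rate above is assumed, so the figures show a mechanism, not an estimate.

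**Conclusion.** The concern holds in a limited form. No masking to session is stated for a pre-post comparison of judged outcomes in a single arm, and baseline scoring that informs allocation or targeting cannot be masked to session. A shift in the rater's threshold could change the number of active language sites with no true change. For a 20% relative fall in calls, the false-positive rate for the count was 0.31 to 0.89, against about 0.05 with no shift. These figures depend on the assumed call rates, activity rule, numbers of targets and patients, and size of shift. A false selective shift away from the tumor is much less likely.

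The reach is narrow: one secondary, exploratory outcome. The feasibility primary outcome is not affected. Motor mapping uses a 50 μV criterion, and fMRI does not depend on this rater. The change is worth making because it is cheap and the article leans on neurophysiology as evidence of effectiveness.

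**What to change.** Add to the language-mapping paragraph under Neurophysiological assessment:

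*For the pre-post comparison, after t4 one neuropsychologist scores each patient's baseline and post recordings in a single random-order batch, with date, session and target labels removed. Where possible, recordings are pooled across patients. The rater is preferably an existing team member who neither did the baseline scoring used for targeting nor treated that patient. Only these scores enter the pre-post comparison; the initial baseline scoring is used for targeting only.*

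If the full protocol already provides for this, one sentence in the article saying so is enough.

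The cost is a second scoring of stored baseline clips and the work of relabeling and shuffling files; no new visit is needed. It can be applied to patients already enrolled if their recordings were kept. If the same person has to score both times, some recall of baseline clips may remain: the minimum of 10 sessions, at up to two per weekday, can be completed in 10 / 2 = 5 weekdays. Using another existing team member, or pooling across patients, reduces this.
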